### Data collection, management, CFPI training, and standardisation

5.10.

Trained study investigators will collect study data, and completed CRFs will be checked for accuracy when entering information into a computer web-based interactive password-protected database administered by Mitchell Institute. On signing consent, participants will be given a unique study identifier, and information collected will be de-identified at source and a study identification used. Programme coordinators will conduct routine quality control. All documentation and case report forms associated with the study will be kept for a minimum of 15 years from the completion of the study. In accordance with the ICH GCP notes for Guidance on Good Clinical Practice, it is anticipated that the data will be stored indefinitely according to the Standard Operating Protocols.

*Training and standardisation:* Staff conducting the study will receive training and relevant documentation and ongoing professional support from the relevant universities (Victoria, Flinders, Notre Dame Universities). Staff delivering the ACIC, PACIC, Heart Foundation, and associated tools will undergo an accreditation process and be assessed as competent against the current standard. In addition, this project requires access to data housed and maintained in hospitals and PHC. Hospital separation data, hospital, and PHC records will be sought. If records are housed within independent services, appropriate consultation will be undertaken with the services themselves. Formalised consent processes as directed by those services will be followed. The potential for variability in data recording is noted and will be standardised by training staff on the ICD-10 classification for CHF and ACC/AHA guidelines for key performance indicators (5, 13–16, 29). Areas of ambiguity will be discussed with at least two members of the steering committee and recorded if there is agreement from both parties.

### Adverse events

5.11.

We do not anticipate any adverse events from this study. All procedures are in place as per local institutions’ guidelines to address issues relating to client dissatisfaction or concerns. Any medical complication will be addressed by the treating physician/institution as part of standard care.

### Expected outcomes

5.12.

The primary outcomes are to achieve concordance in readmission risk between CFPI and SCRinHF, and the number of patient readmissions to the hospital. The secondary outcome is to achieve convergent validity between CFPI and SCRinHF and potential economic cost benefits using the SCRinHF tool.

### Randomisation/blinding

5.13.

Not applicable for Phases 1–3. Trained study staff completing the SCRinHF tool will have access to raw patient data, but be blinded to the patient when completing the tool. Following Phase 3, a focus group will convene to finalise the SCRinHF trial and study tool. Randomisation strategies will be a priority for any future studies.

### Study timelines and follow-up project milestone

5.14.

Study recruitment will commence in September 2021 and end in September 2022 (12 months). A census of all outcome data will be conducted in December 2022. There should be >40 potentially eligible patients over the 12-month recruitment and follow-up period.

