**Methods and analysis:**

*SELFMAN-HF* is a prospective, observational study to evaluate the feasibility and validity of the *SCRinHF* tool, a one-page self-management and readmission risk prediction tool for CHF, with an established, comprehensive CDSM tool. Eligible patients will have CHF with left ventricular ejection fraction <40% and commenced sodium glucose co-transporter-2 inhibitors (SGLT2-i) within 6 months of recruitment. The primary endpoint is the 80% concordance in readmission risk predicted by the *SCRinHF* tool. The study will recruit >40 patients and is expected to last 18 months.

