## Study objectives

3.

The *SELFMAN-HF tests the feasibility and validity of the SCRinHF tool,* comparing the novel one-page tool to the gold standard Flinders Program of Chronic Condition Self-management Tool (CFPI). Feasibility: there are no prior comparisons of short and long form CDSM tools applied to CHF. Validity: first, this will explore comparisons of the SCRinHF to the CFPI in a range of measures including, self-management, clinical progress, and predicting 12 months major cardiovascular outcomes including readmission; and second, the Delphi method to attain peer acceptability and expert consensus on the *SCRinHF* tool.

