### Study population/ recruitment of subjects / setting

5.5.

The study setting of Western Melbourne defined the catchment although recruitment will only take place at community cardiology outpatients and support services for CHF. Recruitment will occur over a 6-month period. Patients identified will be referred to the study case manager for consent, and thetime will then be arranged to review the CFPI, PHQ-9, MLHF, and PACIC. Baseline demographics, tests, and questionnaire scores (Figure 3) will be recorded. All staff will be healthcare workers within community cardiology and aligned services. Participants will be recruited over a 12-month period, from September 2021 to September 2022, and followed for 12 months, ending September 2023. Health staff from primary and tertiary care managing CHF patients will be approached to complete the ACIC, between September 2021 and September 2022.

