### Participant follow-up

5.8.

Clients will be followed up to determine subsequent hospitalisation, major medical events, and interventions at 6 and 12 months. Similar ICD codes for acute CHF will be used for screening information. Data extraction will include a combination of case notes review, medical databases, and contact with PHC and clients directly. Participants requesting changes in answers provided will be discussed at this or any interval to raise this point.

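### The December 2022 census of all outcome data falls before the 12-month follow-up stated elsewhere can be complete, and the stated recruitment period, follow-up and study duration cannot all hold

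*Protocol article*

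**What the plan says.** Section 5.14 sets the data census: "A census of all outcome data will be conducted in December 2022". It also places recruitment between September 2021 and September 2022.

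Section 5.5 gives the same recruitment dates with a later end: "Participants will be recruited over a 12-month period, from September 2021 to September 2022, and followed for 12 months, ending September 2023". Earlier in the same section it says: "Recruitment will occur over a 6-month period". The abstract gives a third duration: "The study will recruit >40 patients and is expected to last 18 months".

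The outcome horizon is 12 months throughout:
- Section 3 describes the validity question as "predicting 12 months major cardiovascular outcomes including readmission".
- Section 5.8 says: "Clients will be followed up to determine subsequent hospitalisation, major medical events, and interventions at 6 and 12 months".
- Section 5.15 projects more than 100 admissions and more than 10 deaths at 12 months.

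Section 5.7 introduces another clock, with the data period running 0 to 12 months from the start of SGLT2-i treatment. Section 4 allows that start to be up to 6 months before recruitment.

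**The concern.** A census that covers every outcome, held about three months after recruitment closes, cannot contain 12-month outcomes for patients who entered late. If it is the data cut for the main results, time at risk depends on the calendar date of entry. Patients with as little as 3 to 4 months of follow-up would be counted alongside patients with the full 12.

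The results at stake are those that need events over 12 months:
- the number of readmissions (a primary outcome in section 5.12);
- concordance in MACE and medical events (one of the primary-endpoint statements in section 5.9);
- predictive validity (sections 2.1 and 3);
- the event rates in section 5.15, which are meant to supply parameters for sizing a later controlled trial. Truncated counts read as 12-month rates would understate them.

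**Working it through.** **Inputs.** Month 0 is taken as 1 September 2021.
- Recruitment length R: 12 months (sections 5.5 and 5.14), or 6 months (section 5.5).
- Follow-up per patient: 12 months (sections 5.5 and 5.8).
- Census time c: month 15 (1 December 2022) to month 16 (31 December 2022), from section 5.14.
- Alternative clock: 12 months from SGLT2-i start (section 5.7), with a lag L of up to 6 months before recruitment (section 4).
- Not stated, so assumed: even accrual over R, and L uniform over 0 to 6 months.

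**Step 1: reproduce the plan's own dates.**
- 12 + 12 = 24 months, ending September 2023. This matches section 5.5.
- 6 + 12 = 18 months, ending March 2023. This matches the abstract's duration but not the calendar dates in section 5.5.
- Neither sum ends by December 2022.

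**Step 2: what needs no accrual assumption.** A patient enrolled at month t has 12 months of post-enrolment follow-up at the census only if t + 12 ≤ c, so t ≤ c − 12 = 3 to 4 months. Nobody enrolled after December 2021 qualifies. With recruitment closing at month 12, the last entrant has 15 − 12 = 3 to 16 − 12 = 4 months.

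**Step 3: share complete under even accrual, (c − 12)/R.**

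| Recruitment | 1 Dec 2022 | 31 Dec 2022 | Lacking 12 months |
|---|---|---|---|
| 12 months | 3/12 = 25% | 4/12 = 33% | 67-75% |
| 6 months | 3/6 = 50% | 4/6 = 67% | 33-50% |

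Of 40 patients, 12-month recruitment leaves about 10 to 13 complete. The share past the 6-month visit is (c − 6)/12, which is 9/12 = 75% to 10/12 = 83%, so 17-25% lack even that visit.

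**Step 4: mean follow-up, capped at 12 months, with 12-month recruitment.**
- 1 December: 0.25 × 12 + 0.75 × (12 + 3)/2 = 3 + 5.625 = 8.6 months.
- 31 December: (1/3) × 12 + (2/3) × (12 + 4)/2 = 4 + 5.33 = 9.3 months.
- Shortfall against 12 months: 1 − 8.625/12 = 28%, and 1 − 9.33/12 = 22%.

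**Step 5: clock from SGLT2-i start.** A patient is complete if t ≤ c − 12 + L. The mean of L is 3.
- 12-month recruitment: (3 + 3)/12 = 50% to (4 + 3)/12 = 58% complete, so 42-50% incomplete.
- 6-month recruitment, with each share capped at 1. On 1 December, half the patients (L below 3) average (3 + 1.5)/6 = 75% complete and the rest are all complete, giving 12.5% incomplete. On 31 December, one third (L below 2) average (4 + 1)/6 = 83% and the rest are all complete, giving 5.6% incomplete.

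The last case brings the incomplete share down to about 6-13%, but it sets aside the calendar dates given in both sections 5.5 and 5.14.

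**The case against.** The strongest reply is that the census need not end data collection. Section 5.14 does not say that it does, section 5.5 carries follow-up to September 2023, and section 5.15 mentions an interim analysis that checks the event modelling. On that reading December 2022 is an early look and no follow-up is lost. This is possible but not established: the interim analysis has no date, nothing links it to the census, and the census is described as covering every outcome. What stands is that the shortfall in follow-up must be stated as conditional on the census being the final cut.

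A reader might also infer that most patients would lack the 12-month outcome. The documents do not support that as a flat statement. It needs 12-month recruitment, roughly even accrual and a clock starting at enrolment. With 6-month recruitment, or with the section 5.7 clock, the share is half or less.

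Nor do the dates undermine the whole comparison of the tools. Section 5.9 also defines the primary endpoint through the readmission risk scored by each tool and their correlation, and section 5.12 names concordance in risk. Both tools are applied to the same patient, so agreement between scores needs no 12 months of events and could be examined in December 2022.

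Finally, "There should be >40 potentially eligible patients over the 12-month recruitment and follow-up period" could be read as squeezing recruitment and follow-up into one 12-month span. It can equally mean a 12-month recruitment and, separately, a follow-up period, so nothing here rests on it.

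**Conclusion.** The contradiction in dates is certain and needs no accrual assumption. Recruitment to September 2022 with 12 months of follow-up cannot yield complete outcomes in December 2022, and the 6-month recruitment period and 18-month duration do not fit the explicit dates.

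The size of the consequence is conditional on December 2022 being the final data cut. Assuming even accrual, the share without 12 months of follow-up is then 67-75% on the explicit recruitment dates (mean 8.6-9.3 months), 33-50% with 6-month recruitment, and 42-50% on the SGLT2-i clock with 12-month recruitment. Only combining that clock with 6-month recruitment brings it to about 6-13%.

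The effect is confined to outcomes that need 12 months of events. Agreement between the two tools' scores is untouched. This is an internal inconsistency in the timeline. It needs correcting because the data cut decides whether the 12-month outcomes exist.

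**What to change.** Reconcile the abstract, section 5.5 and section 5.14 to one timeline: a single recruitment period, a single study duration, and a final outcome census no earlier than the last patient's month 12. On the explicit dates in section 5.5 that is September 2023, 24 months in total. If 6-month recruitment was what was meant, the calendar dates in sections 5.5 and 5.14 must change to match. State whether the 12 months run from enrolment or from SGLT2-i start, since section 5.7 uses the latter.

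If a December 2022 look is kept, label it interim and limit it to recruitment, event-rate checks and score agreement. No 12-month outcome or predictive-validity result should be drawn from it. The article was published in May 2023, after the census date and before the stated end of follow-up, so the sponsor should also say whether the census took place and how its data are used.

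The cost is a set of date corrections and a final analysis about 9 months after the stated census (December 2022 to September 2023). Section 5.5 already implies that wait.

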### Statistical aspects and data analysis

5.15.

The study cohort assesses feasibility, which will allow appropriate parameters to determine sample size power calculations for future studies that will utilise a controlled design. Initial data analysis will investigate the distribution characteristics of each primary and secondary outcome measure and determine either a parametric or semi-parametric statistical approach to main data analysis. A combination of descriptive statistics, linear mixed models, and generalised estimating equations will be used to calculate and present data. If continuous outcome data are approximately normally distributed, then linear mixed models (LMMs) will be used to examine change over time for each measure at intra-and inter-individual levels. If the distribution of outcome data is more amenable to a semi-parametric approach, then we will use generalised estimating equations (GEEs) to calculate an average estimate of the intervention effect for the cohort. Descriptive statistics for baseline demographics and clinical characteristics will be presented as means (standard deviation) for continuous data and count (percent) for categorical data. As an example, the previous publication provides estimates for pilot sample size calculations for categorical data. A future RCT of 200 patients in each arm for effects size of 25% reduction in readmission at 12 months established an event rate of 1,600 readmissions at 12 months (25–50% historical rate at 1 and 6 months), 90% power, and 5% two-sided significance, and 25–75 patients are published recommendations for small to large, standardised effect sizes (30). With the introduction of SGLT-2, the population level effect size is not known, and we have chosen >40 patients with an LVEF <40% and a NYHA class of 2 or 3. The event rates are well documented as 25% for 1-month readmission and 1-year mortality. Follow-up at 12 months predicts >100 admissions and > 10 mortalities. Interim analysis will ensure that this modelling supports the study goals.

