### Aim and scientific hypotheses

2.1.

The *Self-management in Heart Failure Study* assesses the feasibility and validity of a short form *SCRinHF* tool (6), with the established comprehensive *Flinders Program of Chronic Disease Self-management* (Flinders Program or CFPI) (18–21) for participants who were prescribed an SGLT-2 Inhibitor for CHF. In this, we hypothesise: first, guideline level of care as established by Ref. (1, 2, 12–17), and CDSM can be used to enhance the delivery and uptake of guideline-based care (22–26); second, to achieve this, we have to define clinical pathways. In this study, the model of care is based on patients utilising community cardiologists with community-based triage (Figure 1); third, a short form CDSM tool (*SCRinHF*) will improve efficiency in delivering CDSM programmes without compromising clinical outcomes as compared to the CFPI (Figure 2). The *SELFMAN-HF* study thus aims:

To examine the relationship between CDSM and CHF-related health outcomes over a 12-month period. The CDSM tools that will be used are the CFPI and SCRinHF (Table 1). The study will establish the feasibility of use and the concurrent and predictive validity of the SCRinHF when compared to the CFPI in predicting self-management, clinical measures, and predictive measures of health outcomes (hospital readmissions) in CHF and their limitations and strength

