### Study objectives, measures, and endpoints

5.1.

The *SELFMAN-HF* is a prospective, observational case-cohort study, in three phases: *Phase 1,* is defining the geographical boundaries of the community cardiology clinic in Western Melbourne, Australia, *and the* development of appropriate clinical indicators, study design, and registry; *Phase 2,* is the assessment of data and recommendations; and Phase 3, the Delphi methodology process. The measures and endpoints are highlighted for each sub-section.

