### Assessment of study data, measures, recommendations, and intervention (Phase 2)

5.3.

Details of the CFPI, heart foundation cardiovascular chronic disease tools, and patient assessment and chronic illness care satisfaction questionnaire (PACIC) are previously summarised [Table 3 in Iyngkaran et al. (3)] and published (3, 7, 8, 11). The CFPI tool and PACIC will be used to obtain information on patients’ CDSM capacity and patient satisfaction informing the CHF journey over 12 months. The PACIC is in three parts, where self-management assumes a component of the third category. Other study measures include the assessment of participants’ clinical changes in CHF and general wellbeing through the 6-month CFPI score, NYHA class, MLWF and 6MWT, and plasma NT-proBNP (Figure 3). Data on readmissions and mortality will be obtained from patient interviews and, if possible, healthcare records from main health providers, hospitals, primary healthcare (PHC) records, and community cardiac services. Cost–benefit analysis will be determined using standard billing criteria for public hospital funding Medicare Australia. These data will be compared with any ongoing prospective works on the CHF patient journey in Victoria. All enrolled patients will receive routine medical care as per Heart Foundation guidelines 2018 (27, 28). No additional investigations will be required from usual care. Comparing the long form CFPI and short form (*SCRinHF* tool) – trained staff who administer the CFPI will record the time to complete the process. The *SCRinHF* tool (Table 1) will be completed by an independent staff from those who filled in the CFPI. They are blinded to patients and will receive access to raw data on patients. The time to complete this will also be recorded.

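### One cohort scored on both tools cannot yield the GEE intervention effect of section 5.15 or the clinical comparison of SCRinHF with the CFPI hypothesised in section 2.1

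*Protocol article*

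**What the plan says.** **Analysis (section 5.15, Statistical aspects and data analysis).** The choice of model depends on the distribution of each outcome. If it is approximately normal, "linear mixed models (LMMs) will be used to examine change over time for each measure at intra-and inter-individual levels". Otherwise GEE will be used "to calculate an average estimate of the intervention effect for the cohort". The same section says that the cohort assesses feasibility and is to supply parameters for sizing later controlled studies.

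**Hypothesis (section 2.1, Aim and scientific hypotheses).** The third hypothesis is that the short form "will improve efficiency in delivering CDSM programmes without compromising clinical outcomes as compared to the CFPI".

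**Economic outcome (section 5.12, Expected outcomes).** The secondary outcome includes "potential economic cost benefits using the SCRinHF tool". Section 5.3 bases the cost–benefit analysis on public-hospital billing.

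**Design.** Section 5.1 says the study "is a prospective, observational case-cohort study, in three phases". On randomisation, section 5.13 says "Not applicable for Phases 1–3". Section 5.3 says "The CFPI tool and PACIC will be used to obtain information on patients’ CDSM capacity and patient satisfaction informing the CHF journey over 12 months". It also says that the SCRinHF form "will be completed by an independent staff from those who filled in the CFPI", and that these staff work from raw data and are blinded to the patient. The time taken to complete each tool is recorded. The abstract and section 4 require the SGLT2 inhibitor to have been started within six months of recruitment, and section 5.7 sets the data window at 0 to 12 months from that start.

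**The concern.** An intervention effect needs a contrast: patients, or periods, with and without the intervention. A statement that one tool does not compromise outcomes relative to another needs outcomes under each tool. The design provides neither. SCRinHF is a second score on patients who also have the CFPI; it is not described as a separately delivered care pathway. All patients are newly on a drug whose population-level effect in this setting section 5.15 itself calls unknown.

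The LMM and GEE sentences also name different targets. As written, the shape of an outcome's distribution would decide whether a result is reported as change over time or as an intervention effect.

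What is at stake is interpretation. Change over 12 months mixes any self-management effect with the new drug, usual care and the natural course of heart failure. If it carries the label of an intervention effect, it could be read as evidence for the programme or for the short form, and could mislead those who plan the later controlled trial.

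**Working it through.** The article gives no effect size, margin or power for an intervention contrast in this cohort, so there is no figure to reproduce. The check is whether the named quantities can be estimated.

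**Inputs**
- Cohort: more than 40 patients (section 5.15); 40 used here.
- Visits: baseline, 6 and 12 months (sections 5.6 and 5.8).
- CFPI, SCRinHF scoring and SGLT2 inhibitor: all present for every patient (abstract, sections 4 and 5.3).
- No randomisation or control group (sections 5.1 and 5.13).

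**Step 1. Can the tools and the drug be separated?** Write the mean outcome as

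E(Y) = b0 + b1·CFPI + b2·SCRinHF + b3·SGLT2i.

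Each indicator equals 1 in every row, so all four columns are identical. Rank = 1 of 4. Only the sum b0 + b1 + b2 + b3 can be estimated.

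**Step 2. Can an intervention effect be separated from time?** Write

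E(Y) = b0 + g6·V6 + g12·V12 + d·Post,

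where V6 and V12 mark the visits and Post marks any visit after baseline. In all 40 × 3 = 120 rows, Post = V6 + V12. Rank = 3 of 4. Only g6 + d and g12 + d can be estimated, and these are the changes from baseline to 6 and 12 months. Using GEE instead of LMM changes the distributional and correlation assumptions, not this matrix. If time entered as a straight line, d would become separable algebraically, but only because linearity was assumed. The drug would still be unseparated, because no patient is observed off it.

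**Step 3. Is there an outcome difference between the tools?** Patient *i* has one clinical outcome Y_i and one hospital cost C_i, whichever tool is considered. Any within-patient contrast is Y_i − Y_i = 0 and C_i − C_i = 0 by construction, and no second group supplies a between-patient contrast. What does differ within a patient is:
- the two scores, giving agreement and convergent validity;
- how each score relates to later events, giving predictive validity;
- the two completion times, T_CFPI and T_SCRinHF, giving a paired staff cost of (cost per minute) × (T_CFPI − T_SCRinHF).

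**Step 4. Scale of a real comparison (illustration under assumed inputs).** The article states no margin. Assume one-sided 2.5%, 80% power, and equal 12-month event proportions p of 25% to 50% in two arms:

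n per arm = (1.960 + 0.842)² × 2p(1 − p) / margin², with (1.960 + 0.842)² ≈ 7.85.

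| Margin | p = 25% | p = 50% |
|---|---|---|
| 10 points | 7.85 × 0.375 / 0.01 → 295 | 7.85 × 0.5 / 0.01 → 393 |
| 20 points | 7.85 × 0.375 / 0.04 → 74 | 7.85 × 0.5 / 0.04 → 99 |

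The plan has just over 40 patients in total and no arms. The question belongs to the later controlled study.

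**The case against.** The best defence is that the GEE phrase is loose wording. The preceding sentence says change over time, GEE is the fallback for measures that do not suit LMM, and no comparator is described. The article calls its design hypothesis-generating (section 6), leaves controlled comparison to later work, and states operative aims in section 2.1 (feasibility, concurrent and predictive validity) that one cohort can address. This stands as far as severity goes. It does not remove the error, because the two sentences still name different targets and the third hypothesis still asks for a comparison that the design lacks. The comparison with other Victorian work in section 5.3 is unspecified and does not supply a group managed on SCRinHF.

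Some stronger readings are tempting, but the documents do not support them:
- *That the analysis promises a formal test of non-compromise.* Section 5.15 gives no such test or margin; the statement is a hypothesis in section 2.1.
- *That no economic comparison is possible.* Section 5.3 records completion time for both tools, so a paired staff-time cost is available. Only downstream hospital savings are out of reach.
- *That deaths (40 × 25% = 10) will bias a completer analysis.* Section 5.15 does not specify a completer analysis, and mixed models use all available visits.
- *That omitting a regression of outcome on tool score is a gap.* An article may leave that detail to the analysis plan.
- *That the observed change is set to become the trial's effect size.* Section 5.15 speaks only of parameters, and section 6 points to event rates.

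**Conclusion.** The point holds. An intervention effect in this cohort is fully aliased with visit and cannot be separated from the newly started drug. No SCRinHF-versus-CFPI difference in clinical outcomes or downstream hospital cost exists to estimate. This is a matter of identification, so a larger cohort of the same design would not cure it.

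The reach is limited. Agreement, completion time, staff-time cost and each tool's predictive validity are untouched, and within-cohort change can be estimated if it is called that. It should be corrected because it governs what the study may conclude, but it is a correction of target and wording rather than of data collection.

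The conclusion assumes that the CFPI is administered to all enrolled patients and SCRinHF is scored for the same patients, as section 5.3 describes, and that time is modelled by visit.

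**What to change.** 1. **Section 5.15:** replace the GEE target with *average within-cohort change over time, not attributable to CDSM or to either tool*, so that LMM and GEE share one target.
2. **Section 2.1:** restate the third hypothesis as agreement between the tools, predictive validity and administration time. Defer clinical non-compromise to the future controlled study.
3. **Section 5.12:** limit the economic outcome to the staff-time cost of administering each tool, using the completion times already planned in section 5.3.

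The cost is narrower claims. No new data, visits or patients are needed.
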